#### **8.1.6 Analysis of Secondary Endpoints**

##### **8.1.6.1 Analysis of Secondary Efficacy Endpoints**

**8.1.6.1.1** Echocardiographic assessment of valve regurgitation severity at discharge or 30 days, 3 months, 6 months, and 12 months post-surgery will be compared between groups using the Cochran-Mantel-Haenszel (CMH) test.

**8.1.6.1.2** Changes in echocardiographic parameters (right atrial size, right ventricular size, radial value, width of the narrowest part of the regurgitant beam, and area of reverse blood flow) at discharge or 30 days, 3 months, 6 months, and 12 months post-surgery will be compared using the t-test.

**8.1.6.1.3** NYHA cardiac function classification at discharge or 30 days, 3 months, 6 months, and 12 months post-surgery will be compared between groups using the CMH chi-square test or rank-sum test.

**8.1.6.1.4** The risk of reoperative tricuspid valve surgery, performance of the test instrument, and success rate of the surgical technique due to tricuspid valve insufficiency will be compared using the chi-square test or Fisher's exact test.

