##### **8.1.6.2 Secondary Safety Endpoint Analysis**

**8.1.6.2.1** The incidence of device-related serious adverse events (SAEs) at discharge or 30 days, 3 months, 6 months, and 12 months post-surgery will be compared between groups using the chi-square test or Fisher's exact test.

**8.1.6.2.2** The incidence of all-cause mortality at discharge or 30 days, 3 months, 6 months, and 12 months post-surgery will be compared using the chi-square test or Fisher's exact test.

**8.1.6.2.3** The incidence of cardiovascular death related to the test device at discharge or 30 days, 3 months, 6 months, and 12 months post-surgery will be compared using the chi-square test or Fisher's exact test.

**8.1.6.2.4** The incidence of major bleeding related to the test device at discharge or 30 days, 3 months, 6 months, and 12 months post-surgery will be compared using the chi-square test or Fisher's exact test.

**8.1.6.2.5** The incidence of severe damage to cardiac or other body structures related to the test device at discharge or 30 days, 3 months, 6 months, and 12 months post-surgery will be compared using the chi-square test or Fisher's exact test.

**8.1.6.2.6** The incidence of device-related infective endocarditis at discharge or 30 days, 3 months, 6 months, and 12 months post-surgery will be compared using the chi-square test or Fisher's exact test.

**8.1.6.2.7** The incidence of thromboembolic events related to the test device at discharge or 30 days, 3 months, 6 months, and 12 months post-surgery will be compared using the chi-square test or Fisher's exact test.

**8.1.6.2.8** The incidence of adverse events from postoperative to 5-year follow-up will be compared using the chi-square test or Fisher's exact test.

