#### **8.7 Statistical methods for all data, including processing of missing, unused or erroneous data (including dropout and withdrawal) and unreasonable data**

When the main indicators are missing, the last observation value carry-over method (LOCF) is used to fill in the data. Other indicators are analyzed using the actual collected data.

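### The collected-values rule for secondary endpoints leaves deaths and ring failures out of the NYHA, regurgitation and echo comparisons, which can bias those results or hide harm

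*Protocol*

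**What the plan says.** Protocol section 8.7 has two rules. For the primary endpoint: "When the main indicators are missing, the last observation value carry-over method (LOCF) is used to fill in the data". For everything else: "Other indicators are analyzed using the actual collected data". The heading of 8.7 covers dropout and withdrawal, so the second sentence is a stated rule and not a gap left for the SAP.

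Section 8.1.6.1 sets the tests, visit by visit (discharge or 30 days, then 3, 6 and 12 months):
- Regurgitation grade: "post-surgery will be compared between groups using the Cochran-Mantel-Haenszel (CMH) test".
- Echocardiographic changes: "post-surgery will be compared using the t-test".
- NYHA class: "post-surgery will be compared between groups using the CMH chi-square test or rank-sum test".

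None of these gives a place to a patient who has died or a value to one who has been reoperated on. Two other comparisons bear on the point. Section 8.1.6.1.4 compares "The risk of reoperative tricuspid valve surgery, performance of the test instrument, and success rate of the surgical technique" between groups, and section 8.1.6.2.2 says: "The incidence of all-cause mortality at discharge or 30 days, 3 months, 6 months, and 12 months post-surgery will be compared".

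Sections 7.2.4 to 7.2.6 schedule NYHA class and transthoracic echo at 3, 6 and 12 months and cancel no visit after reoperation. Section 7.1.5.3.4 lets the investigator withdraw a patient for complications, adverse events or treatment failure. Section 8.9 runs efficacy analyses on the full analysis set and the per-protocol set.

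**The concern.** A patient who dies has no later NYHA class, regurgitation grade or echo measurement, so even in the full analysis set these become comparisons among survivors. Survivors are no longer the groups that randomisation formed. An arm that loses its sickest patients shows a better average class in those who remain.

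Reoperation works in a similar way by one of two routes. If the patient stays and has an echo, that echo is collected data but describes a second repair or a prosthesis. If the patient is withdrawn, there is no value. The first ring's failure disappears from the regurgitation and echo results either way.

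At stake is the reading of the functional and echocardiographic results, each of which will carry its own p-value in support of the device.

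**Working it through.** **Plan figures.** No stated figure underlies this point; only the arm size of 82 is used below. For reference, the planned 75 per group reproduces: (1.960 + 0.842)² × 2 × 0.95 × 0.05 / 0.10² = 74.6, rounded up to 75. The plan then enrols 82 per arm to allow for dropout. All event counts below are assumptions except where a section is named.

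**Are deaths likely at all?** Section 4.2 describes an MC3 ring series with 4 early deaths among 75 patients. The same proportion would give 82 × 4/75 = 4.4 deaths per arm. This shows that deaths should be expected; it says nothing about an imbalance.

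**Deaths, illustration 1.** Assume 12 of 82 patients per arm would be in class III–IV at 12 months, with 3 deaths on control and 8 on the test ring. Let s be the share of deaths that fall on those patients. The collected-values proportion in class III–IV is (12 − 3s)/79 on control and (12 − 8s)/74 on test.

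| s | Control | Test | Apparent advantage of test ring |
|---|---|---|---|
| 100% | 9/79 = 11.4% | 4/74 = 5.4% | 6.0 points |
| 50% | 10.5/79 = 13.3% | 8/74 = 10.8% | 2.5 points |
| 33% | 11/79 = 13.9% | 9.33/74 = 12.6% | 1.3 points |
| 12/82 = 14.6% (deaths unrelated to class) | 14.6% | 14.6% | 0 |

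With s = 100%, counting death together with class III–IV gives 12/82 = 14.6% in both arms, so the false advantage goes. Fisher's exact test on 9/79 against 4/74 gives p = 0.25.

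**Deaths, illustration 2.** Assume control is 40/28/10/2 in classes I to IV with 2 deaths. The test ring has the same patients, but 0, 2, 4, 6 or 8 more of those in class III–IV die.
- Collected-values share in class I–II on test: 68/80, 68/78, 68/76, 68/74, 68/72 = 85.0, 87.2, 89.5, 91.9, 94.4%. Control: 68/80 = 85.0%. With 2 to 8 extra deaths the apparent advantage is 2.2 to 9.4 points (CMH row-mean-score p from 0.62 to 0.13).
- Death ranked worst (scores 0 to 4): class I–II is 68/82 = 82.9% in both arms, and the mean score is 0.756, 0.780, 0.829, 0.878, 0.927 on test against 62/82 = 0.756 on control. The ordering now points against the ring with more deaths, though not significantly (p = 0.33 with 8 extra deaths).
- If the extra deaths are unrelated to class, the collected-values share stays at 85.0% in both arms. The share of all 82 alive in class I–II falls from 82.9% to 68 × (76/80)/82 = 78.8% with 4 extra deaths, or 68 × (72/80)/82 = 74.6% with 8.

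**Reoperation.** Assume 8 severe recurrences on test and 4 on control, with r of the test patients reoperated and none on control. Control shows 4/82 = 4.9% severe.

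| r | Test, re-echoed as not severe | Test, withdrawn |
|---|---|---|
| 0 | 8/82 = 9.8% | 8/82 = 9.8% |
| 2 | 6/82 = 7.3% | 6/80 = 7.5% |
| 4 | 4/82 = 4.9% | 4/78 = 5.1% |
| 6 | 2/82 = 2.4% | 2/76 = 2.6% |

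The two routes give nearly the same answer. The test ring's true 9.8% is understated as soon as anyone is reoperated, but the ring looks better than control only once more than 4 of the 8 are.

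**The case against.** The strongest case against is that the harm is not hidden from the report. All-cause mortality is compared by arm at the same visits, and freedom from reoperation for tricuspid insufficiency is itself a secondary efficacy endpoint through 12 months. A reader would see 8 deaths against 3. The success criterion in section 8.5 rests on the 6-month primary endpoint alone. Describing function among survivors, with mortality beside it, is a legitimate choice. All of this stands, and it limits the weight of the point. It does not make the NYHA, regurgitation and echo comparisons themselves fair between the arms.

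The illustrated size is also fragile. Six points needs every death to fall in class III–IV and a large imbalance. The protocol excludes NYHA IV, right heart failure and life expectancy under one year, and none of the illustrated differences is significant at 82 per arm. That stands too.

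Three stronger readings are tempting, and the documents do not support them. A reader might infer that reoperated patients are always graded on the second repair; the protocol is silent, and section 7.1.5.3.4 also allows withdrawal. A reader might infer that NYHA class and regurgitation grade are the only efficacy results at 12 months; freedom from reoperation is another. And a reader might infer that the more harmful ring will look better; that holds only if deaths or reoperations are unbalanced and fall on the worse patients.

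Finally, ranking death as worst can blur things as well: in the first illustration, 12/82 in both arms does not show the five extra deaths. That is a reason to add the analysis, not to substitute it.

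**Conclusion.** The point holds in a limited form. Section 8.7 fixes a collected-values rule under which deaths, and failures of the ring that lead to reoperation, leave the visit-by-visit comparisons of NYHA class, regurgitation grade and echo change. Where these events differ by arm and fall on sicker patients, the bias favours the arm with more failures. Where deaths are unrelated to class, the comparison shows equality while fewer patients are alive in good function.

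The documents give no basis for the size. With the assumed 8 against 3 deaths it is 0 to about 6 points, depending on the share of deaths in class III–IV. The primary non-inferiority decision does not depend on this sentence, and the separate mortality and reoperation comparisons would show the harm. This is a cheap improvement to three supporting results, not a threat to the trial's conclusion.

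**What to change.** In sections 8.7 and 8.1.6.1:
1. Keep the collected-values tables and the same CMH or rank-sum tests. Beside them, add an analysis of NYHA class and regurgitation grade in which death is the worst category.
2. In the regurgitation analysis, count reoperation for tricuspid insufficiency as severe regurgitation, as a failure of the ring, from that date on.
3. For the continuous echo changes, do not use values measured after tricuspid reoperation as outcomes of the ring.
4. Show the numbers dead and reoperated by arm beside each visit's result.

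The cost is a few sentences and an added table; sample size, visits and data collection do not change. The drawback is that the added ordinal result mixes death with function, and that a reoperated patient receives a grade that may not have been measured. The collected-values table therefore stays alongside.

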#### **8.8 Report deviations from the planned statistical procedures**

After the final draft of the statistical plan is finalized, if any changes are needed during the statistical analysis, the sponsor, investigator and statistician should agree to make any changes. The statistical analysis report and summary report should clearly specify the additional statistical analysis results.

### **8.9 Selection criteria and reasons for subjects included in the analysis**

Full analysis set (full analysis set, FAS): The collection of all cases randomized to the group and who received surgical implantation devices.

Conformity set (per protocol set, PPS): A subset of the full analysis set, a data set generated by subjects who are fully compliant with the protocol, compliance including treatment received, availability of measurement of primary endpoint indicators, and no significant deviation from the protocol. PPS analysis is used for primary efficacy endpoints.

Safety Dataset (safety set, SS): All actual data that were randomly enrolled and underwent surgical implantation of devices and had post-implant safety metrics recorded. SS analysis was used for primary safety metrics.

Efficacy analysis will be performed on the full analysis set and the compliant set. All baseline demographic data analysis will be performed on the full analysis set and safety evaluation will be performed on the safety set.

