#### **7.1.4.6 Evaluating the Repair Outcome**

During tricuspid valve repair, intraoperative echocardiography is utilized to assess the function of the valve and the quality of the repair. To achieve optimal results, the following steps are critical: accurate measurement of the valve orifice size, proper selection of the Annuloplasty Ring, and optimal implantation technique. If damage to the structures below the valve is detected, additional surgical interventions may be required. After carefully measuring the size, the Annuloplasty Ring is implanted, if direct visual inspection and/or intraoperative testing still indicate that the valve regurgitation is not fully corrected, the surgeon must be prepared to remove the Annuloplasty Ring and perform artificial heart valve replacement during the same surgery.

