### **7.1.6 Efficacy Evaluation Methods**

#### **7.1.6.1 Description of Efficacy Parameters**

Primary efficacy endpoint: The success rate of valve annuloplasty repair at 6 months postoperatively, defined as no severe regurgitation and an increase in diameter  $\leq 15\%$  (based on a comprehensive assessment of regurgitation severity and diameter increase).

Other efficacy endpoints:

**7.1.6.1.1** At discharge or 30 days postoperatively (whichever comes first), 3 months, 6 months, and 12 months:

- Degree of valve regurgitation assessed by echocardiography (evaluated according to the tricuspid regurgitation assessment index table).
- Changes in echocardiographic parameters (right atrial and ventricular size, diameter, width of the narrowest regurgitation jet, and reverse flow area).
- NYHA functional class.
- Freedom from reoperation due to tricuspid valve insufficiency.

**7.1.6.1.2** Evaluation of the trial device's performance, including needle insertion smoothness and user-friendliness of the ring holder.

**7.1.6.1.3** Technical success rate of the surgery (before leaving the operating room), defined as no intraoperative death, successful implantation of the annuloplasty ring, successful removal of the ring holder, and no emergency surgery or secondary

intervention related to the trial device.

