### **7.1.8 Trial Endpoints**

Primary endpoint: The success rate of valve annuloplasty repair at 6 months postoperatively, defined as no severe regurgitation and an increase in diameter  $\leq 15\%$  (based on a comprehensive assessment of regurgitation severity and diameter increase).

Secondary endpoints:

**7.1.8.1** At discharge or 30 days postoperatively (whichever comes first), 3 months, 6 months, and 12 months:

**7.1.8.1.1** Degree of valve regurgitation assessed by echocardiography (evaluated according to the tricuspid regurgitation assessment index table).

**7.1.8.1.2** Changes in echocardiographic parameters (right atrial and ventricular size, diameter, width of the narrowest regurgitation jet, and reverse flow area).

**7.1.8.1.3** NYHA functional class.

**7.1.8.1.4** Freedom from reoperation due to tricuspid valve insufficiency.

**7.1.8.2** Evaluation of the trial device's performance, including needle insertion smoothness and user-friendliness of the ring holder.

**7.1.8.3** Technical success rate of the surgery (before leaving the operating room), defined as no intraoperative death, successful implantation of the annuloplasty ring, successful removal of the ring holder, and no emergency surgery or secondary intervention related to the trial device.

**7.1.8.4** At discharge or 30 days postoperatively (whichever comes first), 3 months, 6 months, and 12 months:

**7.1.8.4.1** Incidence of serious adverse events, including cardiovascular death, major bleeding, severe damage to cardiac or other body structures, infective endocarditis, and thromboembolic events related to the trial device.

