**7.1.8.4.7 Thromboembolic events related to the trial device.**

**7.1.8.5 Device defects.**

**7.1.8.6 Other adverse events.**

## **7.2 Trial Procedures**

### **7.2.1 Screening (within 30 days preoperatively)**

**7.2.1.1** Patients must sign the informed consent form before screening.

**7.2.1.2** Collect demographic data (gender, date of birth, weight, and height).

**7.2.1.3** NYHA functional class, vital signs (blood pressure, pulse).

**7.2.1.4** Laboratory tests: Complete blood count, blood biochemistry, coagulation function, and pregnancy test if necessary.

**7.2.1.5** Electrocardiogram (ECG), echocardiography (TTE or TEE).

**7.2.1.6** Record antiplatelet or anticoagulant medications.

**7.2.1.7** Randomization using a central randomization system.

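### Patients taken to surgery who never receive a ring leave every analysis set, so they cannot count as technical failures, primary failures or deaths

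*Protocol*

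**What the plan says.** Section 8.9 of the protocol defines three sets.

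- **FAS:** "The collection of all cases randomized to the group and who received surgical implantation devices".
- **Per-protocol set (PPS):** a subset of the FAS, so it inherits the same entry condition.
- **Safety set:** "All actual data that were randomly enrolled and underwent surgical implantation of devices and had post-implant safety metrics recorded".

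On their use, 8.9 states that "Efficacy analysis will be performed on the full analysis set and the compliant set", and that "safety evaluation will be performed on the safety set". No set of all randomised patients, or of all patients taken to surgery, is defined.

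Technical success is listed among the efficacy endpoints in 7.1.6.1 and 7.1.8 and compared between arms under the secondary efficacy analyses in 8.1.6.1.4. It is "defined as no intraoperative death, successful implantation of the annuloplasty ring, successful removal of the ring holder", together with no device-related emergency surgery or secondary intervention. All-cause mortality and device-related serious adverse events are safety endpoints (7.1.7.1).

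Section 7.2.1 lists "Randomization using a central randomization system" among the screening steps, so allocation precedes surgery. Section 7.1.4.6 foresees an inadequate repair, after which the surgeon must be ready to "remove the Annuloplasty Ring and perform artificial heart valve replacement during the same surgery". Section 8.1.6.3 counts treatment-emergent adverse events only from implantation onwards.

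**The concern.** Entry to every analysis set depends on an event after randomisation, and the device can influence that event. For technical success, the entry condition is also one of the outcomes being measured: a patient must have been implanted to be counted, yet non-implantation is one of the failures the endpoint exists to detect. For the primary endpoint, a patient whose repair with the allocated ring could not be carried out disappears instead of counting as unsuccessful. For safety, a death on the table before placement reaches neither the mortality rate nor the serious-adverse-event rate.

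At stake are the non-inferiority decision, which is taken on the FAS and PPS against a margin of -10%, and the arm comparison of technical success. If non-implantation is commoner with the test ring, the exclusions favour that ring. If it is commoner with the control ring, they favour the control.

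**Working it through.** **1. Who is in which set under 8.9**

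| Patient | FAS | Safety set |
|---|---|---|
| Operated on, ring never placed | out | out |
| Dies in theatre before placement | out | out |
| Dies in theatre after placement | in | in only if post-implant safety data are recorded |
| Ring placed, then removed for valve replacement (7.1.4.6) | not stated whether this counts as received | not stated |
| Ring placed, holder not removed or device-related re-intervention | in, counted as a technical failure | in if data are recorded |

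The first two rows are certain losses from every set. The third and fourth depend on data recording or on a rule that 8.9 does not give. The last row shows that technical success can still fail inside the FAS.

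**2. The plan's own sample size.** Inputs from 8.2.1: success 95% in both arms, margin 10 points, one-sided alpha 0.025, power 80%. With unpooled variance, n = (1.960 + 0.842)² × 2 × 0.95 × 0.05 / 0.10² = 74.6, so 75 per group. This reproduces the stated figure. Planned enrolment is 82 per group, and the illustrations below use 82.

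**3. Technical success.** *Assumption:* k of 82 patients in an arm are operated on without receiving a ring, and there is no other technical failure. The FAS rate is (82 − k)/(82 − k) = 100% for every k. The rate over all 82 is (82 − k)/82.

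- k = 1: 98.8%
- k = 2: 97.6%
- k = 4: 95.1%
- k = 8: 90.2%

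The overstatement is k/82, or 1.2 to 9.8 points over this range. With two other technical failures and k = 2, the FAS rate is 78/80 = 97.5% and the rate over all 82 is 78/82 = 95.1%.

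**4. Primary endpoint.** Section 8.1.5 specifies the Newcombe two-sided 95% interval. Its lower limit is d − √[(p₁ − l₁)² + (u₂ − p₂)²], where d = p₁ − p₂, l₁ is the Wilson lower limit for the test arm and u₂ the Wilson upper limit for control. *Assumption:* control 78/82, so p₂ = 95.12% and u₂ = 98.09%. Of 82 test patients, k never receive a ring.

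| Excluded (k) | Failures among implanted | FAS as written | Lower limit | Counted as failures | Lower limit | Conclusion changes? |
|---|---|---|---|---|---|---|
| 1 | 4 of 81 | 77/81 | -7.7% | 77/82 | -9.2% | no |
| 1 | 5 of 81 | 76/81 | -9.3% | 76/82 | -10.7% | yes |
| 2 | 4 of 80 | 76/80 | -7.9% | 76/82 | -10.7% | yes |
| 4 | 4 of 78 | 74/78 | -8.2% | 74/82 | -13.7% | yes |

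Worked row (k = 2):

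- As written: p₁ = 76/80 = 95.00%, l₁ = 87.84%, d = -0.12. Lower limit = -0.12 − √(7.16² + 2.97²) = -7.9 points.
- Counted as failures: p₁ = 76/82 = 92.68%, l₁ = 84.94%, d = -2.44. Lower limit = -2.44 − √(7.74² + 2.97²) = -10.7 points.

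**The case against.** Restricting the main analysis to treated patients is common in device trials, and leaving out someone never taken to surgery can be defended. That stands. It does not cover a patient in whom implantation was attempted and failed when implantation is itself part of an endpoint.

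Section 8.1.2 leaves a detailed classification of the sets to a SAP. The SAP could settle how removed rings are handled. The entry conditions themselves are already stated in 8.9, so this is a stated rule and not an omission.

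The protocol's definitions do not support several stronger inferences that a reader might draw:

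- *That all intraoperative deaths and failed repairs drop out.* A death after placement meets the FAS wording, and a recorded death is arguably itself a safety record. A ring placed and then removed arguably counts as received.
- *That technical success is 100% by construction.* Holder removal, device-related re-intervention and death after placement can all register as failures inside the FAS.
- *That the trial cannot show a difference in implantability or operative mortality.* Intraoperative complications and adverse events are recorded on the day of surgery (7.2.2), device defects are an endpoint, and 8.1.2 lists cases by centre. Non-implanted patients should be visible in the case accounting, though not in the rates.
- *That one excluded patient is enough to reverse the result.* With 4 failures among the implanted in each arm, one exclusion does not.
- *That surgeons will withhold a ring knowing the arm.* Masking is not among the bias controls in 7.1.3, but nothing in the protocol suggests arm-dependent decisions. The 30 days in 7.2.1 is an upper bound on the screening window, not a stated gap between allocation and surgery.

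**Conclusion.** The point holds for a defined group: patients taken to surgery who never receive a ring, including those who die before placement. They are outside the FAS, PPS and safety set, so they cannot be technical or primary failures and are missing from the mortality and serious-adverse-event rates. Two further cases are left open: a death after placement without recorded safety data, and a ring removed in the same operation.

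The direction for technical success is upward. The size is unknown because the protocol gives no non-implantation rate. Under the assumptions shown, one to eight such patients in an arm overstate technical success by 1.2 to 9.8 points. Two in the test arm alone can carry the primary lower limit across -10% when failures among the implanted are equal. One can do so only when the test arm already has 5 failures against 4. All primary-endpoint cases assume 82 per arm, 78/82 control successes and no non-implanted control patients.

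**What to change.** Reword 8.9, and carry the wording into the SAP:

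- **FAS:** all randomised patients in whom surgery was started (or all randomised patients), analysed as randomised.
- **Failure rule:** non-implantation, ring removal with conversion to valve replacement, and intraoperative death count as failures of both the primary endpoint and technical success. State that this rule takes precedence over the last-observation-carried-forward rule in 8.7, because these patients may have no postoperative value to carry forward.
- **Technical success denominator and safety set:** all patients in whom implantation was attempted or surgery was started. Delete the requirement for post-implant safety records.

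The cost is a change of definitions with no new data collection, and a few more failures may be counted. Some power may also be lost. *As an assumption*, if 2% in each arm were not implanted, the expected success rate would be 0.95 × 0.98 = 93.1%. Power = Φ(0.10/√(2p(1 − p)/82) − 1.960) would then be 71.4%, against 83.6% at 95%. At 1% non-implantation it would be 77.2%. The change should be made before any outcome data are seen.
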